**Figure 2. F2:**
[figure not shown]
Schematic representation of the study design. Assessments were performed at baseline and after 8 weeks of intervention. 1RM: 1 repetition maximum test; CAT: COPD Assessment Test; CRQ: Chronic Respiratory Questionnaire; ET: elastic tape; ESWT: endurance shuttle walking test; HADS: Hospital Anxiety and Depression Scale; ISWT: incremental shuttle walking test; PAL: physical activity level; PR: pulmonary rehabilitation; PFT: pulmonary function test; V: visit.

### Intervention

#### ET Overview

The ET (Kinesio Brand Tape, Tex Gold), which is made of cotton and elastic material and is skin-colored and waterproof, will be applied by the same trained professional throughout the study to avoid intervention fidelity bias, with the participant in a relaxed, supine position. The individual will lie down on a stretcher so that their torso is extended, thus facilitating the application of the ET [9]. The ET will be positioned at the origins and insertions of the following muscle groups: rectus abdominis, internal oblique, and internal intercostal (Figure 3). These muscle groups were chosen because they are the main muscles involved in forced expiration during exercise, and the tape will always be placed with the maximum possible tension, which is 200% of its original size. The tape will be placed at the beginning of the session and replaced every 7 days. If at least 2 cm of tape is detached, the ET will be replaced regardless of the length of time it has been in place.

**Figure 3. F3:**
[figure not shown]
Illustration of the elastic tape placement protocol. Tape was applied to key expiratory muscle groups—rectus abdominis, internal oblique, and intercostal muscles—using standardized positioning and tension to ensure reproducibility and comfort during the pulmonary rehabilitation sessions.

#### Sham Group

The sham group will receive a nonelastic tape (3M Micropore) placed using an identical procedure to the ET and replaced every 7 days. If at least 2 cm of tape is detached, the tape will be replaced regardless of the length of time it has been in place.

#### PR Program

On the first day, at the start of PR, individuals will be briefed on the benefits of PR, such as reduced dyspnea, additional positive effects on comorbidities, improved HRQoL and overall health, and increased exercise capacity [13]. Additionally, a WhatsApp contact will be provided on the same day for ongoing communication regarding health-related issues. Both groups will undergo an 8-week PR program, including 1-hour sessions twice a week, supervised by a physiotherapist with experience in PR, carried out in the hospital’s outpatient clinic. The program will be individualized and divided into 30 minutes of aerobic training on an ergometric treadmill (Technogym Jog 500) and 30 minutes of resistance training using free weights (dumbbells and barbells) for the upper limbs and gym machines for the lower limbs (LLs). Aerobic training will be performed with a heart rate (HR) corresponding to 50% to 80% of the maximum HR according to the formula proposed by Karvonen et al (HR_training_ =HR_rest_+ [HR_max_–HR_rest_]×% intensity), where HR_training_ is training heart rate, HR_rest_ is resting heart rate, HR_max_ is maximum heart rate, and % intensity is the percentage of training intensity. The intensity will be increased weekly by 5% of the maximum HR until reaching 80% of the maximum HR. Furthermore, this progression of treadmill load will also be guided by the scale of subjective perception of exertion (modified Borg scale) [16]. The training will be carried out in such a way that during each session, the participant must remain on the Borg scale between scores 4 and 6 [17]. The increase in intensity by 5% of the maximum HR will be adjusted after 2 sessions and/or if the score on the Borg scale is less than 4. If the individual reports fatigue greater than 6 on the modified Borg scale, the intensity will be reduced and, in the next session, the increase in intensity will be tried again. The individual may interrupt the activity if they feel symptoms or intense respiratory discomfort, resuming it after improvement. HR, peripheral oxygen saturation (SpO_2_), and the subjective perception of exertion will be monitored during all exercise. Oxygen supplementation will be provided as needed to maintain SpO_2_ of 90% or greater [17].

Resistance training will consist of exercises for the upper limbs through lifting weights with dumbbells and for the LLs via weight machines. Large muscle groups will be trained, including the biceps, deltoids, quadriceps, and hamstrings. Training will begin with 3 sets of 8 repetitions of each exercise at a workload of 50% of the one-repetition maximum [18]. The number of repetitions will subsequently increase to 3 sets of 10 and, later, 12 repetitions. Load progression will be carried out when the individual tolerates performing more than 12 repetitions for each set without compensatory movements and/or symptoms of intolerance. The workload will be increased according to individual tolerance.

Resistance training for the upper limbs will include shoulder abduction and elbow flexion. Resistance training for the LLs will include knee extension and hip extension using “leg press” equipment.

No written material will be provided to either group. Transportation expenses will be subsidized for all individuals to reduce absenteeism and increase feasibility and adherence to the protocol. This financial resource will be funded for this research project. For analysis of the results, individuals must complete at least 80% (13 sessions) of the program, which will be monitored using the PR monitoring form, where data on HR, SpO_2_, the Borg scale, speed, and treadmill incline will be tabulated every 5 minutes, from the beginning to the end of the training session for all sessions.

The acceptability of ET use will be monitored throughout the session based on a visual inspection performed by the physiotherapist at the beginning of the session and during ET replacement every 7 days to immediately identify any skin changes that the individual may experience due to continued ET use.

To ensure or increase adherence to the 8-week PR program, the importance and potential benefits of PR, as established in the literature, will be explained to each participant individually, regardless of the group they are allocated to after randomization. Throughout the PR program, individuals will have a WhatsApp contact available to clarify and assist with any questions regarding their COPD-related health status. In cases of clinical worsening, the individual will be taken to the hospital emergency room for immediate medical care.

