### Analysis of the Population

The inclusion criteria will be as follows: diagnosis of moderate to very severe COPD [1], clinical stability (ie, no exacerbations for at least 30 days), male sex, nonobese status (BMI ≤29.9 kg/m^2^), absence of musculoskeletal limitations, and no participation in another research protocol or a PR program in the past 6 months. The exclusion criteria will be decompensated cognitive, neurological, and/or cardiological dysfunction and receiving home oxygen therapy. An intention-to-treat analysis will be performed using the patient’s most recent assessment in case of study dropout or absence of data and will be treated by imputing the last observation carried forward [14].

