### Experimental Design

Clinical and anthropometric data will be collected during the participant interview. Participants will complete questionnaires to assess health status (COPD Assessment Test [CAT]), HRQoL (Chronic Respiratory Questionnaire [CRQ]), and anxiety and depression symptoms (Hospital Anxiety and Depression Scale [HADS]). Then, a complete pulmonary function test (body plethysmography), the incremental shuttle walking test (ISWT), and the endurance shuttle walking test (ESWT) will be carried out. Finally, individuals will use a triaxial accelerometer (ActiGraph GT9X) for 7 days to assess their PADL. Lastly, individuals will be randomly assigned to 1 of 2 groups: the ET group or the sham group.

At baseline and postintervention, assessments will be performed by a researcher who is not involved in individual recruitment or intervention. After inclusion, individuals will begin an 8-week PR program twice a week (Figure 1). Individuals in the ET group will have the ET placed before the beginning of the PR program, and the ET will be replaced every 7 days throughout the 8-week period. The sham group will receive a nonelastic tape of the same color and size at the same position in the chest wall at the beginning of the PR program, and the tape will be replaced every 7 days, similar to the ET group. At the end of the PR program, participants will repeat the same assessments, except for the ISWT. The ESWT will be performed at the same level established by the ISWT during the initial evaluation (Figure 2).

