#### Statistical Analysis

Data normality will be assessed using the Shapiro-Wilk test, and homoscedasticity will be assessed using the Levene test. Continuous variables will be presented as mean (95% CI) or as medians and IQRs, according to their distribution. Intergroup comparisons will be performed using 2-way ANOVA for repeated measures with Bonferroni post hoc correction or the Kruskal-Wallis test with Dunn test when assumptions are violated. The proportion of individuals not reaching the minimal clinically important difference will be compared using the chi-square test. Within-group effect sizes (Cohen *d*) will be classified as small (0.2), moderate (0.5), or large (0.8). The Spearman correlation coefficient will be used to analyze the associations between changes in ESWT time and changes in CAT, HADS-A, HADS-D, and CRQ scores. Analyses will be conducted according to the intention-to-treat principle, using GraphPad Prism version 5.0, with significance set at *P*<.05.

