One of the strengths of the proposed study is the use of ET throughout the PR period (16 sessions over 2 months), which may improve the HRQoL of individuals with COPD. Furthermore, this is a randomized, controlled, 2-arm, and blinded study, making it the first study to evaluate the potential effects of ET throughout a PR program. Among the study’s limitations is the inclusion of only nonobese male individuals, which followed the same design as previously published studies [9,10]; however, our goal was to minimize bias, so we did not include obese individuals due to the protective effect of obesity on the respiratory mechanics of patients with COPD [30]. Therefore, future studies should include obese individuals and both male and female individuals. The single-center design and the inclusion of individuals who do not use oxygen therapy will make it difficult to generalize the interpretation of the data at the end of the study. The secondary outcomes, such as HRQoL, anxiety, and depression, were classified as exploratory. Therefore, these outcomes were used for a more comprehensive understanding of the intervention’s effects; however, the statistical analysis for these aspects may not have sufficient statistical power to yield definitive conclusions, and the results regarding secondary outcomes should be interpreted with due caution. For this reason, the results for these outcomes should be interpreted as preliminary insights, suggesting the need for future investigations into these outcomes, especially in female participants, as COPD affects both sexes similarly.

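### The 13-session condition for being analysed conflicts with the stated intention-to-treat analysis for participants who attend 12 or fewer sessions, and nothing says which rule governs

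*Protocol article*

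**What the plan says.** The PR Program section sets an attendance condition: "For analysis of the results, individuals must complete at least 80% (13 sessions) of the program". It does not call this a per-protocol set, a sensitivity analysis or a definition of adherence.

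Three other sections point the other way:

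- Analysis of the Population: "An intention-to-treat analysis will be performed using the patient’s most recent assessment in case of study dropout or absence of data", and such cases "will be treated by imputing the last observation carried forward".
- Statistical Analysis: "Analyses will be conducted according to the intention-to-treat principle".
- Sample Calculation: the 20% increase in each group is justified partly by imputation under intention to treat.

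The Experimental Design section fixes the order of events. After the baseline assessments, "Lastly, individuals will be randomly assigned to 1 of 2 groups: the ET group or the sham group"; then "After inclusion, individuals will begin an 8-week PR program twice a week". The Anticipated Findings section gives the total as 16 sessions.

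**The concern.** The number of sessions attended is known only after allocation. A rule that makes it a condition for being analysed is therefore a post-randomisation exclusion. The participants left in each arm are those who kept attending under that arm's treatment, and the two remaining sets need not be comparable.

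Differential attendance is plausible here but not shown. The arms wear different materials, the elastic tape is applied at maximum stretch, and its hypothesised effect is less dyspnoea during exercise. Any of these could affect who stays in the programme.

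What is at stake is the meaning of the primary comparison. With 21 participants planned per arm, leaving out a few can move the estimate. Because both rules are in print, the analysis set could also be settled after the data are known.

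**Working it through.** **1. The threshold.** Two sessions a week for 8 weeks gives 2 × 8 = 16. Then 0.80 × 16 = 12.8, rounded up to 13 (13/16 = 81.25%). Twelve sessions is 12/16 = 75%, below the threshold. The article's figure of 13 reproduces, so the problem is not arithmetic.

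**2. The two rules side by side, by type of participant.**

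| Randomised participant | PR Program rule | Intention-to-treat rule |
|---|---|---|
| 13 or more sessions, week-8 test done | analysed | analysed |
| 13 or more sessions, week-8 test missing | analysed, value imputed | analysed, value imputed |
| 12 or fewer sessions, week-8 test done | excluded | analysed |
| 12 or fewer sessions, week-8 test missing | excluded | analysed, value imputed |

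The rules agree in the first two rows and conflict in the last two. The conflict is confined to participants with 12 or fewer sessions.

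**3. What exclusion would do to the estimate.** In one arm, let q be the share with 12 or fewer sessions, M the mean gain of the attenders, and δ the shortfall of the low attenders against them. The mean of all randomised participants, if all were measured at week 8, is

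(1 − q) × M + q × (M − δ) = M − qδ.

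The attenders-only mean is M, so exclusion raises that arm's mean by qδ. For the difference between arms:

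bias = q_ET × δ_ET − q_sham × δ_sham.

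The article gives neither q nor δ. For illustration, assume δ = 65 s in both arms. This borrows the planned between-group difference in the endurance shuttle walking test (Sample Calculation) as the gap between attenders and low attenders; it is an assumption, not an estimate.

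| q_ET | q_sham | Bias in tape minus sham |
|---|---|---|
| 20% | 0% | 0.20 × 65 − 0 = +13 s |
| 20% | 20% | 13 − 13 = 0 s |
| 0% | 20% | 0 − 13 = −13 s |
| 10% | 20% | 6.5 − 13 = −6.5 s |
| 30% | 10% | 19.5 − 6.5 = +13 s |

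The sign and the size depend entirely on quantities that the article does not give.

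**4. Sample size.** Inputs from Sample Calculation: difference 65 s, SD 65 s, so d = 65/65 = 1.0; alpha 0.05, taken as two-sided; power read as 0.80. The two-sample t-test needs 16.71, so 17 per group. Then 17 × 1.2 = 20.4, so 21. Both planned figures reproduce. At d = 1.0, power is 0.885 with 21 per group and 0.807 with 17.

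**The case against.** The best defence is that the article names intention to treat in three places, including the section that governs analysis. The contrary sentence stands alone in the description of the rehabilitation programme, between the transport subsidy and the attendance form. It may have been meant as an adherence or per-protocol threshold. The Experimental Design section also does not limit the end-of-programme assessments to those with 13 sessions, and a fuller protocol or SAP may define the analysis sets. This makes intention to treat the likelier intention. It does not remove the conflict, because the sentence is an unqualified condition for being analysed and nothing ranks it below the other rule.

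The defence does succeed against several stronger readings that a reader might infer:

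- *That imputation for dropouts would never operate.* A participant with 13 or more sessions who misses week 8 is still in the analysis and imputed under either rule.
- *That attendance is known to differ by arm.* The article has no attendance data. Both arms wear tape, neither is told its allocation, and both receive the same transport subsidy. A skin reaction leads to tape removal and, if unresolved, to removal from the study under the Adverse Events section. That is a separate route to loss, not an effect of the 13-session rule.
- *That the rule would favour the tape by a stated number of seconds.* A figure such as 20% × 65 s is the shift in one arm's mean. It is a between-arm bias only if the other arm's term is zero.
- *That the rule would leave the trial underpowered.* Seventeen per group is the number that the trial is powered for, and the 20% allowance covers a fall to it. Nor can 0.885 be set beside the bias example: it needs the full 65 s in everyone. With 20% of the tape arm falling 65 s short and the SD held at 65 s, the all-randomised difference is 65 − 13 = 52 s, d = 0.8, and power at 21 per group is 0.716.

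**Conclusion.** The contradiction is real and follows from the text alone. For a randomised participant with 12 or fewer sessions, one sentence excludes and three sections retain, and no order of precedence is given. Applied as written, the attendance rule would replace the randomised comparison with one conditioned on post-randomisation behaviour.

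The documents do not show that the primary analysis will exclude anyone, and they give no basis for a bias in a particular direction. The 13 s example rests on two assumptions: exclusions of 20% in the tape arm only, and a 65 s shortfall. Other equally permissible inputs give zero or a negative value. No claim about lost power is made.

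The point still needs correcting and is more than missing detail, because a stated rule, if followed, changes what the primary result estimates.

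**What to change.** Remove the 13-session condition as a rule for inclusion in the analysis. State in its place that:

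- the primary analysis includes every randomised participant in the assigned arm, whatever the number of sessions attended;
- week-8 assessments are sought from all randomised participants, including those who attend few sessions or stop the programme;
- the 13-session threshold serves only to describe adherence and to define a per-protocol set for a sensitivity analysis labelled as such.

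This brings the PR Program section into line with Analysis of the Population, Statistical Analysis and Sample Calculation. Seeking week-8 tests from low attenders matters in its own right. Outcomes are assessed only at baseline and after the programme, so for someone without a week-8 test the last observation is the baseline value.

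The cost is a sentence or two of text and a little follow-up effort; the resulting estimate may be less favourable than one from attenders only. With 10 of the planned 42 participants (2 × 21) recruited by November 2025, the change can still be made before most week-8 visits.

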### Assessment Tools

#### Primary Outcome Measure: Functional Exercise Capacity

The ISWT will be performed to assess functional exercise capacity. In this test, individuals will be instructed to walk in a 10 m corridor delimited by cones (with a 9 m distance between them), and the speed will be determined by a beep recorded on the sound box, which increases the speed by 0.17 m/s every minute, with a total of up to 15 stages. They will also be instructed to walk at a speed that allows them to reach the cones when the beep sounds, and at the end of each minute, an additional signal will be given to alert them to the increase in speed [19]. The test will end when the participant is more than 0.5 m away from the cone, reports chest pain, reports severe dyspnea, reports fatigue, reports exhaustion, or requests to stop. The distance walked at the end of the test will be registered for subsequent analyses [20]. Before and after the exercise tests, SpO_2_ and HR will be assessed via a portable pulse oximeter positioned on the individual’s dominant hand (WristOx2 3150; Nonin). Blood pressure (BP) will be assessed via a stethoscope (Littman) and a sphygmomanometer calibrated on the dominant arm (Aneroid Premium - G-Tech).

The criteria for stopping the test will include diastolic BP (DBP) above 140 mm Hg, sustained elevation of systolic BP (SBP) above 240 mm Hg, motor incoordination, feelings of imbalance, mental confusion, clinical manifestations of respiratory distress that worsen with increasing load, dyspnea disproportionate to the intensity of the effort, progressive claudication of the LL, and limb exhaustion [12]. Individuals will be instructed not to consume beverages containing caffeine for at least 12 hours before the test and not to perform intense exercise 24 hours before.

The ESWT will be performed 40 minutes after the end of the ISWT, using the same structure; that is, the volunteers will be instructed to walk in a 10m corridor limited by cones (with a distance of 9 m between them), and the speed will be determined by a sound signal recorded by the cell phone. In this case, the speed will be determined using 85% of the maximum speed reached in the ISWT and will be constant throughout the test [12]. Individuals will be monitored before and after the test, and the interruption criteria will be the same as those used in the ISWT procedure.

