#### Sample Calculation

The sample size calculation was based on the primary outcome, based on a previous study showing a mean difference of 65 (SD 65) seconds between groups in the ESWT [29]. Thus, considering an alpha of .05 and a beta of .80, the estimated sample size will be 17 individuals per group. To account for potential losses and to allow for data imputation under the intention-to-treat principle, the sample size was increased by 20% in each group. Therefore, the final estimated sample size was 21 participants per group.

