## Discussion

### Anticipated Findings

The use of ET during rest periods does not alter lung volume; however, during exercise, individuals with COPD under the same workload (isoload) have shown a notable decrease in tidal volume, minute volume, dyspnea, and TAA. Furthermore, individuals using ET have shown a significant increase in oxygen consumption, workload, and maximal exercise duration compared with those not using ET. Additionally, ET increased the amount of time spent in moderate and vigorous physical activity, along with a marked reduction in sedentary time. As the measurements were randomly performed with or without ET, these data strongly suggest that ET attenuated the ventilatory demand required for exercise performance across individuals [9].

Recently, Santos et al [10] demonstrated that ET use for 21 consecutive days does not alter PADL but reduces dyspnea and improves health status and HRQoL in individuals with moderate to very severe COPD in the short term. Therefore, this new, low-cost intervention also improves COPD symptoms during its continuous use. The use of ET may enhance the already-known effects of the PR program, such as increased exercise capacity and improved quality of life among individuals with COPD.

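### The primary-outcome section presents the ISWT, which is never repeated after the programme, while the schedule, sample size and correlation analysis all point to ESWT time

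*Protocol article*

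**What the plan says.** All references are to the protocol article.

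- **Primary Outcome Measure: Functional Exercise Capacity.** The section begins: "The ISWT will be performed to assess functional exercise capacity". After describing the incremental test it adds: "The distance walked at the end of the test will be registered for subsequent analyses". The endurance test comes later in the same section, 40 minutes after the ISWT, and for it "the speed will be determined using 85% of the maximum speed reached in the ISWT and will be constant throughout the test". The section does not say what result of the ESWT is recorded, or which of the two tests is primary.
- **Experimental Design.** On follow-up: "At the end of the PR program, participants will repeat the same assessments, except for the ISWT". It continues: "The ESWT will be performed at the same level established by the ISWT during the initial evaluation".
- **Sample Calculation.** The basis is given as follows: "The sample size calculation was based on the primary outcome, based on a previous study showing a mean difference of 65 (SD 65) seconds"; the test named there is the ESWT.
- **Statistical Analysis.** The sentence on between-group comparisons names no outcome. The correlation analysis uses the change in ESWT time. No analysis names ISWT distance.
- **Abstract, Methods.** Both walking tests are listed for exercise capacity, with no ranking.

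**The concern.** The section that should fix the primary endpoint presents a test that is done only before randomisation. Distance in the ISWT is the one test result it sets aside for analysis, and that result has no follow-up value. Someone who takes the endpoint from its own section arrives at a variable on which the arms cannot be compared. Someone who takes it from the sample size arrives at ESWT seconds, which the primary-outcome section never declares.

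What is at stake is the clarity of the trial's main pre-specified commitment. A primary endpoint should be readable from the section that defines it, with its variable, unit and time point. It should not have to be inferred from other sections against that text.

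A smaller inconsistency follows. The 40-minute interval after the ISWT can be observed at baseline but not at week 8, when there is no ISWT. The baseline ESWT comes after a symptom-limited test on the same structure, and the follow-up ESWT does not.

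**Working it through.** **1. The sections side by side**

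| Section | ISWT | ESWT |
|---|---|---|
| Primary Outcome Measure | Named first; distance kept for analysis | Described; no result variable named |
| Experimental Design, baseline | Done | Done |
| Experimental Design, after the programme | Not repeated | Repeated at the baseline-set level |
| Sample Calculation | No difference or SD in metres | Difference 65 s, SD 65 s |
| Statistical Analysis | Not mentioned | Change in ESWT time, in the correlations |

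Only the first row is out of line with the others.

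**2. What can be estimated for the ISWT**

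Planned participants: 2 × 21 = 42. Planned follow-up ISWT values: 0. Neither a change from baseline nor a week-8 comparison between arms exists, and the planned repeated-measures ANOVA cannot be run on it. The last-observation-carried-forward rule under Analysis of the Population does not help. Applied to the ISWT, it would give every participant a change of exactly zero.

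**3. The stated sample size**

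Inputs from Sample Calculation: "a mean difference of 65 (SD 65) seconds between groups in the ESWT", alpha 0.05, and a beta of 0.80, which I read as power 0.80. Sidedness is not stated; I assume two-sided. Equal allocation is inferred from the equal group sizes.

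- Standardised difference: d = 65/65 = 1.0.
- Normal approximation: n = 2(1.960 + 0.842)²/d² = 2 × 7.85 = 15.7, so 16 per group.
- Two-sample t-test: n = 16.71, so 17 per group. This is the article's figure.
- Power by t-test: 0.807 at 17 per group, 0.885 at 21.
- Allowance for losses as the article applies it: 17 × 1.2 = 20.4, so 21 per group.

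The figure reproduces. The arithmetic alone does not identify the test, because any outcome with d = 1.0 gives 17. What ties it to the ESWT is that the section names that test and works in seconds. With no ISWT difference or SD anywhere in the article, a sample size for ISWT distance cannot be computed.

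**4. The 40-minute rule**

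Both arms have an ISWT before the baseline ESWT and none before the follow-up ESWT. The difference in conditions is common to the arms, so it need not bias the contrast between them. It does enter every baseline-to-follow-up comparison within an arm. The within-group effect sizes would be affected, and so could the proportions judged against the minimal clinically important difference, if these are counted on change in ESWT time.

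**The case against.** The best defence is that the endpoint can be identified. Sample Calculation bases its figures on the primary outcome and gives them in ESWT seconds. Experimental Design repeats the ESWT, and Statistical Analysis uses change in ESWT time. The heading of the disputed section names a construct, functional exercise capacity, and both tests sit under it. No sentence states outright that ISWT distance is the primary endpoint. The ISWT may come first simply because it is done first and sets the ESWT speed, and keeping its distance for later analysis is compatible with describing the sample at baseline.

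Much of this stands. The design is coherent: one ISWT to set the speed, then the ESWT before and after. What does not stand is that the text is therefore adequate. The defining section presents a different test, names that test's result and leaves the ESWT without one.

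The defence also rules out several stronger readings that a reader might infer:

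- *The trial has no analysable primary endpoint, or its schedule and sample size disagree.* They agree; both point to the ESWT, which is measured before and after and is powered for.
- *Two tests under one heading allow the endpoint to be chosen later.* A test without follow-up values cannot be chosen later to show a treatment effect.
- *Tape must be off at the follow-up ESWT.* Anticipated Findings does report, from an earlier study, longer "maximal exercise duration compared with those not using ET". But the Objective and the Introduction ask about additional effects of tape used with rehabilitation and do not confine the question to performance without tape. The tape condition at testing is also a detail that the full protocol may settle.
- *The registry entry is wrong.* The record is not part of the documents, so no mismatch can be seen.

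**Conclusion.** The point holds as an internal contradiction about the primary endpoint. The primary-outcome section presents the ISWT, for which 0 of 42 planned participants will have a follow-up value. The schedule, the sample size and the correlation analysis all point to ESWT time. The defect lies in how the endpoint is declared. The stated 17 and 21 per group are not affected.

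The conclusion about the ISWT rests on the text alone. Reproducing the sample size rests on two assumptions: a two-sided alpha, and a beta of 0.80 meaning power of 0.80.

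The mismatch over the 40-minute interval is real but secondary. It touches within-group results and need not bias the comparison between arms.

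**What to change.** In Primary Outcome Measure: Functional Exercise Capacity:

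1. State that the single primary endpoint is ESWT endurance time, in seconds, at week 8, walked at the speed set at baseline and compared between arms with adjustment for baseline ESWT time. The baseline value is already collected, so the adjustment needs no new data. The gain in precision depends on the correlation between baseline and week-8 times, which the article does not give.
2. Describe the ISWT as a baseline-only test that sets the ESWT speed, and take its distance out of the primary-outcome definition. It can stay as a baseline descriptor.
3. Reconcile the 40-minute instruction with Experimental Design by saying what, if anything, precedes the ESWT at follow-up.

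The cost is a wording amendment. The visits and the 21 per group stay as they are. The Results section reports 10 participants recruited by November 2025 and expects results by November 2026, so the wording can be settled before outcome data are analysed.
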